### Paradoxical intention intervention

Each participant will undergo a 4-week paradoxical intention treatment. The decision to use a 4-week intervention period was based on a review of previous studies, where the typical duration for PI treatment was around four sessions.^9^ The intervention will be delivered via the internet through four weekly modules, with each module containing educational texts, instructions for minor exercises and homework assignments.

The first week’s module provides an overview of the treatment as well as information about insomnia, and exercises. It introduces the rationale behind the paradoxical intention technique and guides participants in how to implement the technique in the upcoming week. In the second module, participants will find information about common challenges encountered while applying the paradoxical intention technique. This module also offers support and ongoing encouragement to use the technique nightly. The third module continues with troubleshooting advice for any issues that may arise and further encourages participants to persist with the technique. The final, fourth module focuses on relapse prevention. Here, patients will receive information about maintaining their progress and strategies to respond to any potential setbacks. The 3-month follow-up will require participants to complete the set of measures outlined in table 2. A 3-month follow-up was selected to balance the need for assessment of longer-term effects while also minimising attrition which is critical given the smaller pilot sample. Few prior studies on PI have included follow-up assessments.^9^ The duration chosen was considered to be proportionate to the length of intervention, allowing for evaluation of the sustained effects without excessive participant drop-out.

**Table 2 T2:** Overview of the study instruments and survey timepoints

Domain	Instrument	Inclusion screening	Baseline	W1	W2	W3	W4	FU 3 months
Insomnia outcome measures	ISI	x	x	x	x	x	x	x
Secondary outcome measures	Sleep diary	x	x		x		x	x
Secondary outcome measures	DASS-21		x		x		x	x
Secondary outcome measures	WSAS		x				x	x
Secondary outcome measures	BBQ		x				x	x
Proposed mechanisms	SAS		x		x		x	x
Proposed mechanisms	GSES		x		x		x	x
Proposed mechanisms	MCQ-I		x		x		x	x
Proposed mechanisms	SPAQ		x		x		x	x
Satisfaction with treatment	CSQ						x	
Expectations and credibility	CEQ			x				
Adverse effects	NEQ						x	
Eligibility screening, demographic information and informed consent	Constructed items	x						
Items on previous treatments, participants’ experience and engagement in treatment	Constructed items	x					x	

BBQ, Brunnsviken Brief Quality of life; CEQ, Credibility and Expectancy Questionnaire; CSQ, Client Satisfaction Questionnaire; DASS-21, Depression Anxiety Stress Scale-21; FUfollow-upGSES, Glasgow Sleep Effort Scale; ISI, Insomnia Severity Index; MCQ-I, Metacognitions Questionnaire-Insomnia; NEQNegative Effects QuestionnaireSAS, Sleep Anxiety Scale; Sleep diaryideographic sleep diarySPAQ, Sleep Problem Acceptance Questionnaire; WweekWSAS, Work and Social Adjustment Scale

### Qualitative interviews

Qualitative interviews will be conducted following the treatment, wherein 10–15 participants will be invited for interviews about the treatment. The exact number will be determined during the process, based on when information saturation has been achieved.^28^ These interviews, which can be carried out either in person or via videocalls, are not conducted by the treatment providers in order to mitigate the risk of social desirability bias from the participants. The interviews will be audio-recorded and transcribed for subsequent analysis using thematic analysis. The focus of these interviews will explore specific aspects such as participants’ sleep patterns during the treatment, their experiences with paradoxical intention, and various elements like text volume, therapist support and homework assignments. Questions will explore how these elements influenced their sleep quality and adherence to the treatment. Follow-up questions will probe deeper into their personal experiences, challenges faced and suggestions for improvement. To select interviewees, participants will be asked if they wish to partake in qualitative interviews and among those who consent, a selection will be made with the purpose of achieving a variety of expressed voices, for example, a variety of ages, genders and clinical outcomes represented.

### Measures

The timepoints of the different assessments used are summarised in table 2 following the Standard Protocol Items: Recommendations for Interventional Trials (SPIRIT) requirements. The full SPIRIT checklist with extended answers is provided in online supplemental material 1. All measures were either previously validated in Swedish or were translated from a validated language version to Swedish using back-translation.^29^

#### Primary outcomes

The ISI^30^ will be the primary outcome measure. The ISI is a 7-item scale that assesses the severity of insomnia symptoms. Each item is scored on a 5-point Likert scale, with higher scores indicating greater insomnia severity. The total score helps categorise the severity of insomnia (eg, no insomnia, subthreshold, moderate or severe).

#### Secondary outcomes

The following additional outcome areas will be measured: sleep diary parameters (ie, sleep onset latency, sleep regularity, sleep efficiency and sleep duration). Data from sleep diaries are recorded daily by the participants on the web platform, where averages are computed to assess sleep patterns. Depression and anxiety will be measured with the Depression Anxiety Stress Scale-21. Each item is rated on a 4-point scale, and scores are summed to yield a total score for each domain.^31^ Functional impairment is measured with the Work and Social Adjustment Scale (WSAS)^32^ which contains five items that evaluate functional impairment due to psychological or physical problems in work, social life and leisure activities. Each item is scored on an 8-point scale with higher scores indicating greater impairment. Quality of life will be measured with the Brunnsviken Brief Quality of life measure (BBQ).^33^ The BBQ contains 12 items that assess quality of life across various domains, such as learning, creativity and leisure. Items are rated on a 5-point scale with higher scores indicating better quality of life. To minimise participant fatigue, the WSAS and the BBQ will not be measured at mid-point of treatment (week 2).

#### Mechanisms and predictors

The following mechanisms of change will be measured. Sleep-related performance anxiety (Sleep Anxiety Scale; SAS).^12^ The SAS is an 8-item scale measuring anxiety specifically related to sleep. Items are rated on a 3-point scale with higher scores reflecting greater sleep-related anxiety. Sleep effort will be measured with the Glasgow Sleep Effort Scale,^34^ a 7-item scale assessing the extent of effort exerted to initiate or maintain sleep. Items are rated on a 3-point scale, with higher scores indicating more effort regarding sleep. Sleep Problem Acceptance Questionnaire^35^ is an 8-item scale that evaluates acceptance of sleep difficulties and willingness to engage in life despite them. Items are rated on a 7-point scale with higher scores indicate greater acceptance and less avoidance of sleep issues. Metacognitions Questionnaire-Insomnia Short Version,^36^ a 20-item scale that assesses metacognitions related to sleep and insomnia and its consequences. Items are rated on a 4-point scale; higher scores indicate more dysfunctional metacognitions. To investigate predictors for PI, the following areas will be assessed and screened at pre-treatment: sociodemographics (ie, age, gender, educational attainment, marital status and employment status), insomnia symptoms, use of other sleep treatments (eg, pharmacological), and psychiatric comorbidity and medical comorbidity (assessed using sections of the MINI clinical interview^37^ as well as self-reported prior diagnoses).

#### Additional measures

To analyse treatment acceptability and credibility, the Credibility and Expectations Questionnaire (CEQ),^38^ which is a 6-item measure that assesses participants’ expectations and perceived credibility of the treatment on a 9-point scale with higher scores suggesting greater belief in treatment efficacy and higher expectations to improve, will be measured at week 1 following the first module.

Additionally, the Client Satisfaction Questionnaire (CSQ)^39^ will be administered at post-treatment. The CSQ is an 8-item measure of satisfaction with treatment. Each item is rated on a 4-point scale where higher scores indicate greater satisfaction with the treatment offered. Finally, the Negative Effects Questionnaire (NEQ),^40^ a 20-item self-report measure assessing any negative effects experienced during treatment, including the client’s belief about whether these effects were treatment-related or due to external factors, and the extent of their negative impact will be administered once at post-treatment.

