## Methods and analysis

### Participants and procedures

This planned pilot trial without control condition aims to recruit 40 individuals with insomnia disorder through advertisements in newspapers, clinics and university-related settings across Sweden including campuses and social media. The sample size was determined based on recommendations for single-group pilot studies, which typically suggest 20–25 participants.^26^ Considering potential attrition of approximately 25% during the study period,^27^ and the uncertainty regarding the magnitude of effect sizes of PI for the primary outcome (ISI) and the mediators,^9^ we determined that 40 participants would be appropriate to achieve our aims of assessing the effects, acceptability and feasibility of the trial in preparation for a potential larger scale controlled trial. To be eligible for this trial, participants will undergo three screening phases that consist of first, a questionnaire on the web; second, a telephone interview with a structured assessment of inclusion and exclusion criteria using a standardised format, conducted by clinical psychologists or last year master students in psychology; and finally, the completion of a sleep diary (7 days). The criteria used for inclusion and exclusion in the three screening phases are based on expert recommendations for a standard research assessment of insomnia and the Diagnostic and Statistical Manual of Mental Disorders, Fifth Edition (table 1); noteworthy is that all forms of insomnia will be allowed in the study, including comorbid insomnia, which is more common than insomnia without other comorbid disorders.^1^

**Table 1 T1:** Inclusion and exclusion criteria

Inclusion criteria	Exclusion criteria
Insomnia disorder (according to DSM-5 criteria) with or without psychiatric comorbidity	Severe depressive episode with suicidal intentions or actions
Age over 18Swedish resident and Swedish language proficient	Recent changes in psychopharmacotherapy (within the last 3 months) or use of ‘as-needed’ hypnotic medications during the trial
	Current or past diagnosis of psychotic or bipolar disorderCurrent substance use disorder

DSM-5Diagnostic and Statistical Manual of Mental Disorders, Fifth Edition

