Following screening, the individuals offered to be part of the study will be presented with informed consent forms via the internet therapy platform and given the chance to ask questions verbally and in writing before signing. The participants who sign the informed consent form will be given baseline measures including checks for therapy credibility and expectancy and questions about concomitant treatments. Weekly outcome and process measures will follow in combination with treatment and at termination, checks for treatment adherence, treatment compliance and adverse events will take place. Throughout the 4-week treatment, weekly short (15 min or less) meetings with a therapist will take place via phone or videocalls. These meetings have the intention of offering individual support on the use of PI as well as attempting to solve any issues the participant might face with regard to implementing PI correctly.

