### Data analysis

All primary and secondary outcome data will be analysed using linear mixed models which are able to handle missing data and dependency well.^41^ The analyses will follow a stepwise approach, first examining changes from baseline to postintervention to assess the effects of the PI treatment. Then, changes from postintervention to follow-up will be analysed to determine whether the effects are maintained over time. The mixed-models approach will be used to estimate parameters, selecting the best-fitting model based on information criteria comparisons. An alpha level of 0.05 will be used as the criterion for statistical significance. Missing data will be treated as ‘missing at random’ using intent to treat analysis. As the planned study is a pilot, primary and secondary outcomes are only to be interpreted as preliminary results.

Regarding the process measures and proposed mechanisms, the SPSS macro MEMORE for repeated measures bootstrap analysis with multiple proposed mediators^42^ will be employed to investigate baseline to postintervention changes on the proposed mediators (sleep performance anxiety, sleep effort, acceptance and metacognitions) of significant pre-intervention to postintervention primary outcomes. Baseline and postintervention scores for a significant primary outcome measure (Y) and each proposed mediator (M) will be entered with (X) representing the interval of time between measurements. Bias-corrected and accelerated (BCa) bootstrap confidence intervals will be employed. Mediation is significant if the 95% BCa for the indirect effects does not include zero.^43^

The mediational analyses will also explore if different predictors, such as baseline insomnia severity, comorbidity and other patient characteristics, may affect this relationship as time-invariant covariates.

Descriptive statistics such as the percentage of participant attendance and dropout rates as well as the mean and distribution of CEQ and NEQ will be used to analyse the quantitative outcomes of acceptability, feasibility and credibility. Significance levels will be set at p<0.05 for all quantitative statistics tests and effect sizes (Cohen’s d) will be calculated.

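### Negative effects (NEQ) and satisfaction (CSQ) are scheduled once, at week 4, so participants lost before then risk being absent from both results

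*Protocol article*

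**What the plan says.** Under Additional measures, the NEQ description closes with "the extent of their negative impact will be administered once at post-treatment". For satisfaction, the same section says that "the Client Satisfaction Questionnaire (CSQ)^39^ will be administered at post-treatment". Table 2 agrees: each form has one mark, at W4, and none at W1 to W3 or at the 3-month follow-up.

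Under Participants and procedures, the article adds that "at termination, checks for treatment adherence, treatment compliance and adverse events will take place". It does not say whether termination means the scheduled end of the 4 weeks or also the day on which an individual stops. The weekly therapist meetings are described there as support in using the technique; recording negative effects is not among their stated purposes.

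Under Data analysis, acceptability, feasibility and credibility are to be described by "the percentage of participant attendance and dropout rates as well as the mean and distribution of CEQ and NEQ". No denominator is given, and the CSQ is not named in that sentence. The missing-at-random statement stands in the paragraph on mixed models for primary and secondary outcomes.

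On expected loss, the sample size paragraph reads "Considering potential attrition of approximately 25% during the study period".

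**The concern.** Acceptability is one of the four areas that the study sets out to address, and adverse events are listed among the treatment-related aspects to be investigated. The results are meant to shape the treatment and to inform a decision on a randomised trial. The article also presents the technique as possibly more acceptable than a first-line therapy that has trouble retaining patients. What participants who leave would have reported bears directly on that argument.

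The ISI is measured every week, and the DASS-21 and the mechanism scales also at baseline and week 2. A missing week 4 value on those scales can be informed by earlier ones. The NEQ and CSQ have no earlier value. A participant who gives no week 4 answer contributes nothing to either, and the planned mixed models cannot recover what was collected at no other time. If those who do not answer differ from those who do, the summaries are selective, and an analysis plan written later cannot supply the data.

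**Working it through.** **1. Inputs from the protocol article**

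- Planned sample: 40 (Participants and procedures).
- Expected attrition: about 25% over the study period (same section). The share lost by week 4 is not given.
- NEQ and CSQ: one collection each, at week 4 (Additional measures; Table 2).

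**2. The plan's own figure**

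The article starts from a pilot recommendation of 20–25 participants and allows for 25% attrition. Inflating by N / (1 − 0.25):

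- 20 / 0.75 = 26.7, rounded up to 27
- 25 / 0.75 = 33.3, rounded up to 34

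Neither is 40. The article does not present 40 as the output of a formula, however; it adds an unquantified allowance for uncertain effect sizes. So 40 is a judgement and not an arithmetic error. It is used here only as the number starting.

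**3. How many forms could be missing**

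40 × 0.25 = 10 missing, leaving 30. The 25% includes loss up to the 3-month follow-up, so 10 is the ceiling on the plan's own figure. As a milder case, assume 4 missing, leaving 36.

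**4. Bounds on the proportion of all 40 with a negative effect**

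With x events among the responders and m non-responders:

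- best case (no non-responder affected) = x / 40
- worst case (every non-responder affected) = (x + m) / 40
- width = m / 40, whatever x is

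The article gives no expected event rate, so x is assumed over a range.

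| Missing m | Observed x / responders | Best case | If half of m affected | Worst case |
|---|---|---|---|---|
| 10 | 3/30 = 10% | 3/40 = 7.5% | 8/40 = 20% | 13/40 = 32.5% |
| 10 | 6/30 = 20% | 6/40 = 15% | 11/40 = 27.5% | 16/40 = 40% |
| 10 | 9/30 = 30% | 9/40 = 22.5% | 14/40 = 35% | 19/40 = 47.5% |
| 4 | 4/36 = 11% | 4/40 = 10% | 6/40 = 15% | 8/40 = 20% |

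The width is 10/40 = 25 percentage points with 10 missing and 4/40 = 10 points with 4 missing.

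**5. Comparison with sampling error**

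The two-sided 95% exact (Clopper-Pearson) interval for 3/30 is 2.1% to 26.5%. The worst case of 32.5% lies above it, so an ordinary interval on responders would not cover the uncertainty from non-response. For 4/36 the interval is 3.1% to 26.1%, and the worst case of 20% lies inside it. The problem therefore depends heavily on how many forms are missing at week 4.

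**6. What fuller collection would give**

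With no events observed, the upper limit of the two-sided 95% interval is 11.6% for 0/30 and 8.8% for 0/40.

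**The case against.** The strongest reply is that the article nowhere excludes early stoppers from the week 4 forms. Stopping the treatment is not the same as not answering: participation is online from home, an intent-to-treat analysis is claimed (though in the mixed-model paragraph), and a check at termination can be read to cover a person's own early stop. This stands. A reader might infer that early stoppers will be missing; the documents support only a risk of that.

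Second, leavers are not absent from all acceptability results. Attendance and dropout rates count them, and the CEQ is taken at week 1. The weekly ISI and the week 2 DASS-21 could also show worsening before a later dropout. This stands too, but these measures do not record negative effects as such, satisfaction or reasons for leaving.

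Third, a single retrospective NEQ is not in itself a defect, since the form asks about the whole treatment. Agreed; the weakness lies only in who is there to answer it.

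Fourth, it is tempting to say that those who leave are the likeliest to be harmed or dissatisfied. The documents give no reasons for dropout and do not support this. The bounds do not depend on it.

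Fifth, the interviews might be read as leaving out non-completers. The listed selection criteria are only examples, within an aim of varied voices, so that reading fails.

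Finally, handling of withdrawals may be set out in a fuller protocol or in the supplementary checklist, neither of which is shown. That is possible. But the single administration is a stated schedule, repeated in text and table, and not a detail left open.

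**Conclusion.** The point holds as a risk of selective results in two measures. As scheduled, the NEQ and CSQ depend on one collection at week 4, and nothing in the article provides for participants lost before then beyond an undefined check at termination.

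Uncertainty about the proportion with a negative effect reaches at most 25 percentage points on the plan's own attrition figure, and 10 points if 4 forms are missing. These sizes rest on three assumptions: that leavers do not answer, that the event counts are as assumed, and, for the upper bound, that every non-responder was affected. They also use a proportion, whereas the plan states a mean and distribution for the NEQ.

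The primary ISI analysis is not affected. The change is worth making because it protects a stated aim of the pilot at little cost.

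**What to change.** - **Additional measures and Table 2:** state that the NEQ and CSQ are also requested when a participant stops treatment or misses the week 4 form. Under Participants and procedures, say whether the check at termination includes an individual's early stop.
- **Weekly therapist calls:** add a line to the call script so that reported negative effects are recorded at calls that already take place.
- **Data analysis:** name the CSQ alongside the NEQ. Report both with the number answering out of all who started, and give best-case and worst-case bounds for the proportion with a negative effect.

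Naming non-completers in the interview sampling would be a useful option, but the point does not depend on it.

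Cost: a trigger on the platform, one line in the script, and a few extra forms sent to leavers, some of which will not come back. No new instrument or visit is needed.

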### Data analysis

All primary and secondary outcome data will be analysed using linear mixed models which are able to handle missing data and dependency well.^41^ The analyses will follow a stepwise approach, first examining changes from baseline to postintervention to assess the effects of the PI treatment. Then, changes from postintervention to follow-up will be analysed to determine whether the effects are maintained over time. The mixed-models approach will be used to estimate parameters, selecting the best-fitting model based on information criteria comparisons. An alpha level of 0.05 will be used as the criterion for statistical significance. Missing data will be treated as ‘missing at random’ using intent to treat analysis. As the planned study is a pilot, primary and secondary outcomes are only to be interpreted as preliminary results.

Regarding the process measures and proposed mechanisms, the SPSS macro MEMORE for repeated measures bootstrap analysis with multiple proposed mediators^42^ will be employed to investigate baseline to postintervention changes on the proposed mediators (sleep performance anxiety, sleep effort, acceptance and metacognitions) of significant pre-intervention to postintervention primary outcomes. Baseline and postintervention scores for a significant primary outcome measure (Y) and each proposed mediator (M) will be entered with (X) representing the interval of time between measurements. Bias-corrected and accelerated (BCa) bootstrap confidence intervals will be employed. Mediation is significant if the 95% BCa for the indirect effects does not include zero.^43^

The mediational analyses will also explore if different predictors, such as baseline insomnia severity, comorbidity and other patient characteristics, may affect this relationship as time-invariant covariates.

Descriptive statistics such as the percentage of participant attendance and dropout rates as well as the mean and distribution of CEQ and NEQ will be used to analyse the quantitative outcomes of acceptability, feasibility and credibility. Significance levels will be set at p<0.05 for all quantitative statistics tests and effect sizes (Cohen’s d) will be calculated.

The qualitative data from post-treatment interviews will be analysed using thematic analysis.^44^ Initial codes will be generated and grouped into larger themes depending on the emerging data. The number of qualitative interviews will be about 10 depending on when information saturation is reached.

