### Purpose and significance

The most recent meta-analysis supports PI as an effective intervention for insomnia disorder. However, some important aspects of PI have been insufficiently examined, including a modern high-quality assessment of its efficacy, its mechanisms of change and whether patient characteristics predict the treatment effects. The present uncontrolled pilot trial assesses the preliminary efficacy of this treatment on the Insomnia Severity Index (ISI) and secondary outcomes such as quality of life, depression and anxiety. This evaluation serves as groundwork for a possible larger scale randomised controlled trial. It is the first study to examine the effects of PI on insomnia severity using the ISI as well as to comprehensively evaluate secondary outcomes.

While Cognitive Behavioural Therapy for Insomnia (CBT-I) is the preferred first-line treatment for insomnia, there are accessibility issues which prevent many patients from receiving it.^1^ Additionally, research has shown challenges in retaining patients in CBT-I treatments.^25^ In this context, it should be pointed out that PI for insomnia was originally intended for patients who had not improved sufficiently after behavioural interventions for insomnia.^5^ At face value, PI offers a simple, scalable and possibly more acceptable treatment alternative, with a focus on eliminating the behaviours and beliefs that disrupt sleep without demanding greater changes in sleep habits such as sleep restriction. Additionally, there has been a call for increased research into the cognitive aspects of insomnia due to the scarcity of studies in this area.^22^ Consequently, this study could provide practitioners with new methods for the psychological management of insomnia.

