This project aims to evaluate PI for insomnia by addressing four key areas: first, the preliminary efficacy of PI on sleep at post-treatment and 3-month follow-up; second, potential mediators of change to identify which processes are altered during PI that may influence treatment outcomes; third, patient characteristics that could moderate the response to PI; fourth, the acceptability and feasibility of PI as perceived by patients. Specifically, the pilot study will assess the immediate and sustained impact of PI on primary (Insomnia Severity Index; ISI) and secondary outcomes, including functional impairment, quality of life, depression, anxiety and sleep diary parameters. Additionally, it will investigate treatment-related aspects such as compliance and adverse events, explore the proposed mechanisms behind PI’s efficacy, determine the influence of patient characteristics on treatment outcomes and capture participants’ perceptions of PI through qualitative interviews.

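### Aim 3 concerns response by patient characteristic, but the only stated analysis adjusts for mediators and depends on a significant primary result; its first-named predictor, baseline ISI, is prone to regression to the mean

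*Protocol article*

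**What the plan says.** Under Purpose and significance, the protocol article names as one of its four key areas "third, patient characteristics that could moderate the response to PI". The same section also words this as a plan to "determine the influence of patient characteristics on treatment outcomes", and as a gap about "whether patient characteristics predict the treatment effects". Mechanisms and predictors lists the variables, introduced by "To investigate predictors for PI, the following areas will be assessed and screened at pre-treatment": sociodemographics, insomnia symptoms, other sleep treatments, and psychiatric and medical comorbidity.

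Under Data analysis, "All primary and secondary outcome data will be analysed using linear mixed models", and no patient characteristic is named for those models. The mediation analysis is a two-wave model: baseline and post scores of the outcome and of each mediator "will be entered with (X) representing the interval of time between measurements". It examines mediators "of significant pre-intervention to postintervention primary outcomes". The single sentence on patient characteristics belongs to this mediation analysis, which will explore whether predictors "such as baseline insomnia severity, comorbidity and other patient characteristics, may affect this relationship as time-invariant covariates".

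**The concern.** The aim is about response. The sentence that is meant to serve it is about mediation: the relationship it refers to is the path from time through the mediators to the outcome. Three consequences follow.

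- **A different quantity.** The outcome equation of the mediation model holds mediator change fixed. A characteristic that makes PI work better by lowering sleep effort, for example, has that part of its effect removed.
- **A condition.** If mean ISI change is not significant, the mediation model is not run and the aim has no analysis. A null average change is a case in which differences between patients could be of most interest.
- **An artefact-prone first predictor.** Baseline insomnia severity is named first, yet baseline ISI is subtracted to form ISI change. Error in the baseline score enters both sides of the regression with opposite sign.

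The Discussion counts the focus on predictors as a strength, and the results are meant to inform a possible randomised trial. A spurious severity effect, or a missed characteristic, could carry over into that trial's design.

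**Working it through.** **Inputs.** From Participants and procedures: 40 participants, about 25% attrition, one arm. From Data analysis: alpha 0.05 (two-sided assumed) and four mediators. Completers: 40 × 0.75 = 30. The baseline-post correlation r of the ISI, its reliability and the mediator effects are not given, so all of these are assumed and shown as ranges. The plan has no figure of its own on this point to reproduce.

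**Step 1: what the covariate estimates.** With two waves, the time × W term in a random-intercept mixed model equals the coefficient of W on the difference score. A numerical check on complete data gave -0.296 (SE 0.119) from both. A time-invariant covariate in a difference-score equation is therefore a covariate-by-time effect. In the outcome equation of the mediation model, mediator change is also in the regression, so the coefficient is the part of the response that does not run through the mediators.

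**Step 2: what is missed.** The simulation used 2,000 runs, one mediator, a two-level W with equal probability, mediator-to-outcome slope 1 and residual SD 1 in both equations.

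| How W acts | Test | n=30 | n=40 |
|---|---|---|---|
| Shifts mediator change by 1 SD | total ISI change on W | 44% | 58% |
| Same | W in mediator-adjusted outcome equation | 5% | 5% |
| Same | W in equation for mediator change | 74% | 86% |
| Shifts ISI change directly by 1 SD | W in mediator-adjusted outcome equation | 70% | 86% |
| Changes the mediator-outcome slope | additive W | about 5% | about 6% |
| Same | W × mediator-change term | 64% | 80% |

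The first row agrees with a hand calculation. The residual SD of total change is √(1+1) = 1.41, so the SE of the group difference is 2 × 1.41/√30 = 0.52, and 1/0.52 is about 1.9 standard errors.

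**Step 3: baseline ISI as predictor, unadjusted.** Take equal variances at both waves and the same true change for everyone. Then corr(baseline, change) = -(1-r)/√(2(1-r)) = -√((1-r)/2), with slope r-1. Rejection rates are from 20,000 simulated trials.

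| r | correlation | n=30 | n=40 |
|---|---|---|---|
| 0.4 | -0.55 | 90% | not tabulated |
| 0.5 | -0.50 | 83% | 93% |
| 0.6 | -0.45 | 72% | 84% |
| 0.7 | -0.39 | 58% | 72% |
| 0.8 | -0.32 | 41% | 52% |
| 0.9 | -0.22 | 22% | 29% |

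**Step 4: does mediator adjustment remove it?** Step 3 is not the planned model, so the test was repeated in a difference-score model with four mediators, each entered as change and as mean, and no differential response. At n=30 baseline ISI was falsely significant in about 45% to 76% of trials for reliability 0.6 to 0.8. A wider set of assumptions (reliability 0.5 to 0.8, within-occasion error correlation between outcome and mediators 0 to 0.5) gave 26% to 79%. The size varies with the assumptions, but adjustment does not bring the rate near 5%.

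**Step 5: the screening ISI.** Table 2 shows a separate ISI at inclusion screening. If its error is independent of baseline error, it is falsely significant in about 5% of trials. If the errors correlate, the rate in the unadjusted test at n=30 (reliability 0.6 to 0.8) rises to 8-11% at error correlation 0.3, 14-22% at 0.5 and 22-41% at 0.7.

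**The case against.** The strongest reply is that response is in fact tested. A reader might infer from the term time-invariant covariate that a constant characteristic cancels out of a within-person model, so that the aim has no test at all. Step 1 shows that this is wrong: the covariate on the difference score does test differential change, and it finds a direct effect well (70% at n=30). An effect through a mediator also shows in the mediator-change equation, if the characteristic is entered there. What stands is narrower: the outcome equation gives response net of the mediators, and no test of total response is stated.

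A reader might also take it as certain that baseline ISI will look predictive. The document gives no baseline-post correlation, and at r = 0.9 the rate at n=30 is 22%. It is a risk whose size is assumed.

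A third tempting reading is that the listed characteristics exhaust the degrees of freedom. Four mediators as change and mean plus an intercept use 9 parameters and leave 21 of 30, and about nine covariates entered together would leave at most 12. The article does not say that they enter together, so this is not held against it.

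Finally, the analysis is labelled exploratory, outcome results are called preliminary, and a fuller plan may exist. That lowers the severity. It does not remove the point, because the article itself assigns the characteristics to a model that does not answer the aim as stated.

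**Conclusion.** The point holds as a mismatch between a stated aim and the analysis stated for it, and should be fixed before the data are analysed. The primary ISI analysis is unaffected. Total ISI response by characteristic is not directly tested, and what is tested depends on a significant primary result. The detection figures in Step 2 rest on an illustrative effect of one residual SD. Baseline ISI is likely to appear predictive with no true differential response: about 22-90% of trials at n=30 unadjusted (assumed r of 0.9 to 0.4), and about 45-76% in the four-mediator model (assumed reliability of 0.6 to 0.8).

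The word moderate also promises more than the design can give. With no control arm, an association between a characteristic and ISI change may reflect natural course or non-specific factors, which the Discussion concedes cannot be separated from PI. The trial can identify predictors of change during PI. It cannot identify moderators of the effect of PI.

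**What to change.** 1. Add characteristic × time terms to the ISI mixed model, one characteristic at a time, for a short list named in advance from Mechanisms and predictors (for example severity, psychiatric comorbidity, concurrent sleep medication, age and gender). Run them whether or not the primary result is significant, and report estimates with 95% confidence intervals as exploratory.
2. Do not use baseline ISI to predict change from baseline ISI. Use the inclusion-screening ISI, and state that it removes the artefact fully only if screening and baseline errors are independent, and otherwise reduces it.
3. Reword Aim 3 from moderating the response to predicting change during PI.

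The covariates may stay in the mediation model as a secondary exploration. The cost is wording and a few extra models, since every variable is already collected. The downside is imprecision: even with 40 complete cases, the total-response test found a one-residual-SD shift acting through a mediator in only 58% of runs, so wide intervals should be expected and a non-significant term should not be read as no difference.
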